##### Study Procedures

After enrollment, participants complete a baseline survey and are randomized (1:1) to 1 of 2 study arms: coach-based MEI or SOC. Randomization to the intervention arms is stratified by site; age group, to yield a balanced randomization between younger (aged 15-19 years) and older (aged 20-24 years) age groups; and enrollment site.

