The PUSH study uses a built-in randomization engine adapted from previous studies [89]. The allocation between intervention and control arms is determined randomly by the engine, where each round comprises 2 intervention and 2 control assignments that are linked to the stratification factors of site and age group. Once a round is completed, a new round begins.

Participants are asked to participate in research visits at 0, 3, 6, 9, 12, and 18 months (exit interview). This visit schedule aims to ensure frequent contact and to minimize attrition. Laboratories and study-related activities are described in Table 2. Surveys provided at baseline (Textbox 1) are re-administered at each follow-up with additional questions focused on ART, PrEP, barriers, and facilitators to adherence.

**Table 2 table2:** Study visits and associated laboratory tests.

Tasks	Visits					
	Baseline	3 months	6 months	9 months^a^	12 months	18 months
Complete a survey	✓^b^	✓	✓	✓	✓	Exit interview
Provide blood for HIV-1 RNA viral load testing (aim 2) or HIV-1 antibody testing (aim 3)	✓	✓	✓	—^c^	✓	—
Provide urine for drug testing	✓	✓	✓	—	✓	—
Update locator information	✓	✓	✓	✓	✓	—
Meet with MEI^d^ coach (intervention only)	✓	✓	✓	✓	✓	✓
Medical chart review (research staff only)	✓	✓	✓	✓	✓	✓
Compensation, US $	50	50	50	10 check-in via phone; 25 survey	50	25
Participate in an in-depth interview (selected participants)	✓	—	✓	—	✓	—
Compensation, US $	25	—	25	—	25	—

^a^9-month visit constitutes either a brief phone check-in (5 min) or in-person survey (15 min).

^b^Data collected at this time point.

^c^Data not collected at this time point.

^d^MEI: mobile-enhanced intervention.

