#### Data Analysis

Aim 1 analyses are descriptive and include baseline characteristics related to sociodemographic characteristics, HIV infection, and sexual behavior of the YBLMSM and YBLTW samples across all sites as well as stratified by site. Descriptive tables with unweighted estimates and Pearson chi-squared tests for significance are used to compare age, web-use and venue attendance, and other characteristics of each recruited seed type.

To compare the efficiency of *seeds* from direct versus indirect seed selection in the recruitment of HIV-positive or at-risk youth, we use the RDS statistical package developed by Schonlau and Liebau [90]. This permits an assessment of the overlap of networks across seed types and across recruitment sites. Efficiency is assessed through recruitment diagnostics, including coupon return rate, homophily, the mean number of recruits, and recruitment depth per seed type. This approach also allows us to assess the time from recruitment activation through the achievement of target sample size and response rates. RDS weights will not be utilized in these analyses, as this aim focuses on descriptive sample proportions rather than producing population-based estimates. We will also examine the networks described by younger (aged 15-19 years) and older (aged 20-24 years) participants recruited from different *seeds* and use similar methods to understand the overlap of age groups across different networks.

The primary outcome for aim 2 is durable viral suppression (HIV viral load<200 copies/mL), and the secondary outcome is retention in HIV care (defined as documented 2 or more follow-up medical visits over 12 months, treated as a dichotomous variable). The primary outcome for aim 3 is self-reported PrEP use over 12 months in PrEP users, and the secondary outcome is self-reported condom use in PrEP nonusers. The overall approach is based on an intention-to-treat analysis with treatment assignment (eg, coached-based MEI vs SOC) being the primary independent variable for all models.

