The success of the randomization process is measured by comparing the distribution of participant characteristics between the 2 groups at baseline. If the randomization process does not result in comparable groups, adjustment is made for group differences in the multivariable models. For aim 2, logistic regression is used to examine whether participants who receive MEI coach are more likely to be virally suppressed as well as retained and engaged in HIV care than participants in the SOC arm. Generalized estimating equations (GEE) are used to determine whether treatment assignment predicts differences in retention for the coached-based MEI versus the SOC groups using repeated measurements over a 12-month period. GEE is used for the longitudinal data as it adjusts for the intra-personal correlation of repeated measurements on the same individual and provides an estimate of the standard error that is robust to misspecification of this correlation structure.

For aim 3, to evaluate whether YBLMSM and YBLTW receiving coached-based MEI have greater uptake of PrEP over 12-months, a survival model is used to examine whether intervention assignment is associated with time to PrEP use. GEE is used to determine whether treatment assignment predicts differences in PrEP utilization and adherence over time for the coached-based MEI versus SOC groups using the repeated measures over the 12-month period [91]. For both aims, we explore trends in uptake and adherence to treatment or PrEP for the intervention group compared with the control group by including an interaction term between time from randomization and treatment assignment.

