Going beyond the intention-to-treat approach, we will develop multivariate models stratified by age group (aged 15-19 years and 20-24 years) and include potential confounders and predictors such as prior exposure to case management and PrEP, sexual risk (low vs high), and other demographic variables. Additional models will be evaluated for possible dose-response relationships considering a measure of the level of engagement with the intervention and the frequency of app use. We will assess whether receiving coached-based MEI results in decreased substance use severity, by examining changes in mean CRAFFT scores (a measure of substance use severity) over time for the intervention group compared with the control group for each aim. CRAFFT scores will be treated as continuous dependent variables, and the models will adjust for intra-personal correlations between repeated measurements. Multivariate linear regression will be used to test for decreased severity at each follow-up visit, while controlling for identified confounders.

Modeling techniques have been selected based on the capacity to adequately handle the missingness of data. GEE models assume that the missingness is because of a missing at the random mechanism, which is a restrictive assumption. To address dropout, we use inverse probability weighting to relax this assumption of missing at random [92,93]. Other types of missing data will be handled using multiple imputations.

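### Covariate adjustment is triggered by observed baseline imbalance, so the final model depends on the data, and the randomization strata would almost never enter it

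*Protocol article*

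**What the plan says.** The protocol article randomizes 1:1 in both trials. Under Study Procedures for aim 2 it states: "Randomization to the intervention arms is stratified by site; age group, to yield a balanced randomization" across ages 15-19 and 20-24; aim 3 uses the same scheme. Data Collection for Aims 2 and 3 gives the mechanism: "each round comprises 2 intervention and 2 control assignments that are linked to the stratification factors of site and age group". This is permuted blocks of four within strata.

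In Data Analysis, the approach is intention to treat, with "treatment assignment (eg, coached-based MEI vs SOC) being the primary independent variable for all models". The section then says: "The success of the randomization process is measured by comparing the distribution of participant characteristics between the 2 groups at baseline". The rule that follows is: "If the randomization process does not result in comparable groups, adjustment is made for group differences in the multivariable models". It gives no threshold for comparability and does not say which characteristics are compared.

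Other predictors are named only for additional models described as going beyond intention to treat: "we will develop multivariate models stratified by age group (aged 15-19 years and 20-24 years"). Site is not named in any outcome model.

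**The concern.** Under properly executed randomization, baseline differences between arms arise by chance, so comparing them does not measure whether randomization succeeded. It is also a poor way to choose covariates, because imbalance says nothing about whether a variable predicts outcome.

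Two consequences follow. First, the rule works against the design. The factors balanced by stratification are those that should be in the model regardless, yet they are the least likely to look imbalanced. Second, the covariate set is settled only after the arms have been compared. Odds ratios, and hazard ratios if the aim 3 survival model is a proportional hazards model, change in size when a prognostic covariate is added even without confounding. The reported effect could therefore vary with a chance event. At stake are prespecification, interpretability and some efficiency. The validity of the test is not at stake.

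**Working it through.** **1. The plan's own figures.** Sample Size Considerations: 240 × 0.85 = 204 (aim 2) and 225 × 0.80 = 180 (aim 3), as stated. The 85% power depends on the within-person correlation ρ, alpha and sidedness, none of which the article gives. At an assumed two-sided 5%, a single binary outcome of 24% vs 40% with 100 per arm gives 68.2% power. Averaging three visits multiplies the effective n by 3/(1 + 2ρ). At ρ = 0.5 that is 1.5, so 150 per arm and 84.7%, close to the stated 85%. For aim 3 (15% vs 29%, 90 per arm), the same steps give 62.2% for a single outcome and 79.6% at ρ = 0.5.

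**2. Can the strata trigger adjustment?** With blocks of 2 and 2, the arms differ by at most 2 within any stratum. Taking 3 sites × 2 age groups, an age group spans 3 strata and so differs by at most 6. In aim 2 with 120 per arm and half in each age group (assumed), the worst case is 63 vs 57:

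z = (6/120) / √(0.5 × 0.5 × 2/120) = 0.050/0.0645 = 0.77

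This is far below 1.96.

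**3. Can other variables enter by chance?** For k independent characteristics screened at 5% (assumed), P(at least one) = 1 − 0.95^k:

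| k | Probability |
|---|---|
| 5 | 23% |
| 10 | 40% |
| 20 | 64% |

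**4. Does the estimate move?** The aim 2 rates imply a marginal odds ratio of (0.40/0.60)/(0.24/0.76) = 2.11. Keep those rates and adjust for a perfectly balanced standard-normal covariate with an assumed log odds ratio of 0.5, 1.0 or 1.5 per SD. The conditional odds ratio becomes 2.19, 2.43 or 2.81.

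**5. What does omitting the strata cost?** Simulation: 3,000 trials per scenario, 3 sites × 2 age groups, blocks of four, one binary outcome, logistic Wald test at two-sided 5%. The strength of site and age is assumed. Monte Carlo standard error is about 0.4 points for type I error and 0.9 for power.

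| Trial | Strength (extreme-site OR, age OR) | Type I, unadjusted / strata-adjusted | Power, unadjusted / strata-adjusted |
|---|---|---|---|
| Aim 2, N=204 | none | 4.8% / 5.0% | 67.9% / 68.7% |
| | moderate (2.7, 1.65) | 4.8% / 5.6% | 70.8% / 72.8% |
| | strong (5.0, 2.2) | 3.8% / 4.7% | 69.8% / 74.5% |
| | very strong (11, 3.3) | 3.2% / 5.0% | 70.5% / 77.5% |
| Aim 3, N=180 | none | 4.1% / 4.5% | 61.9% / 62.3% |
| | moderate | 4.2% / 4.7% | 62.5% / 64.1% |
| | strong | 4.5% / 5.7% | 63.5% / 66.8% |
| | very strong | 3.5% / 5.6% | 62.3% / 68.2% |

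Adjusting only for variables imbalanced at p<0.05 among 10 screened behaved like no adjustment. Aim 2 power was 67.5%, 70.5%, 69.7% and 70.1% across the four strengths, and type I error was 3.3% to 4.8% over both aims.

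**The case against.** **The strata are not excluded.** Treatment is called the primary independent variable, not the only one, and the text speaks of multivariable models. This is a condensed article, and a full covariate list may sit in an analysis plan that is not shown. That stands: a reader might infer that site and age are left out of the primary models, but the documents do not say so. What remains is that the trigger is stated text and, followed as written, would not bring them in.

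**The test is not shown to be conservative, nor is power shown to be lost.** Both depend on site and age being prognostic. With weak or moderate strata the differences are close to simulation error. This stands too, so the size can only be given conditionally.

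**Strong baseline predictors do not add to the conservatism.** A reader might take all the outcome variance explained by strata and baseline predictors together and compute the size of the unadjusted test as 2(1 − Φ(1.96/√(1 − R²))), giving 3.9% at R² = 0.10 and 2.8% at 0.20. Only variance explained by factors balanced by design counts. In a separate simulation (40,000 runs, N=204, 24% event rate), omitting an unstratified covariate left type I error at 5.1% (R² 0.10) and 4.6% (R² 0.21). Such predictors add power when adjusted for, but leaving them out does not make the test conservative.

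**Predictors are not wholly unused.** Prior PrEP exposure and sexual risk are named for the additional models, and CRAFFT is analysed as change over time, which uses its baseline value. The age-stratified models are likewise secondary, and the article claims no age difference from them. This is fair, and it is why the age point below is minor.

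**Conclusion.** The concern holds in a limited form. The article states an adjustment rule that depends on the observed baseline data, selects covariates by chance imbalance, and is almost certain to pass over the stratification factors. The firm harm is to prespecification and to the interpretation of a conditional odds or hazard ratio. The 40% figure assumes 10 independent characteristics screened at 5%.

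The efficiency loss is conditional. It is about 0 to 2 power points if site and age are weak or moderate predictors and about 3 to 7 if strong, for a single binary outcome at two-sided 5%. The documents give no figure for their strength. Type I error fell to 3.8% and 3.2% for aim 2 only in the strong and very strong cases, and to 3.5% for aim 3 in the very strong case. The triggered rule did not inflate type I error in any scenario, so a reader should not infer an invalid test. The change is worth making but is not critical.

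**What to change.** - Delete the imbalance trigger in Data Analysis. Keep the baseline table as description only.
- Include site and age group in every primary model in both aims.
- Add a short fixed list of baseline covariates already collected for all participants. For aim 2: log10 viral load and new versus prior diagnosis. For aim 3: prior PrEP use. For the CRAFFT models: baseline CRAFFT.
- Leave out the HIV incidence risk index. The measures list restricts it to males, and aim 3 enrols transgender women, so it would be missing by design for some participants.
- Report standardized (marginal) proportions by arm alongside the model estimate. These match the percentages used in the sample size and do not shift in meaning with the covariate set.
- Secondary point: rest any claim that the effect differs by age on a treatment-by-age-group interaction in one model. Separate age-group models do not test that difference.

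The cost is wording only, with no new data. It should be settled before the arms are compared.

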#### Sample Size Considerations

We aim to recruit up to 2000 YBLMSM and YBLTW to be screened for eligibility for aims 2 and 3. We conservatively estimate that 15.00% of the RDS recruited sample will be HIV-infected and not virally suppressed, given an HIV prevalence of 25% to 40% among YBLMSM and YBLTW across the sites and as many as 60% of HIV-infected YBLMSM are undiagnosed [4,9].

We expect a 15.0% loss to follow-up over 1 year in aim 2. Starting with n=240 will yield an effective sample size of 204 individuals in total, or 102 in each group, available for analysis in aim 2. A total estimate of n=200 will be enough to detect an average increase in the viral suppression proportion over the 3 follow-up visits of 16.0% from 24.0% assumed in the control arm to 40.0% in the coached-based MEI arm (odds ratio, OR 2.03), assuming a power of 85.0%. We expect a slightly greater loss to follow-up (20.0% loss to follow-up) in participants in aim 3. Starting with n=225 will yield an effective sample size of 180 individuals in total or 90 in each group. We estimate that a total of 180 participants (90 per group), and assuming a 15.0% average rate on PrEP in the control arm, we can detect an average increase of 14.0% to 29.0% (OR 2.31) with power 85.0%. Lost to follow-up estimates are based on the team’s prior work with this population.

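### Aim 2: the powered quantity (suppression averaged over 3 visits), the primary outcome (durable suppression) and the named model (logistic regression) do not agree, so the stated 85% power does not belong to the analysis named for the primary outcome

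*Protocol article*

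**What the plan says.** All references are to the protocol article.

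- **Sample Size Considerations.** "A total estimate of n=200 will be enough to detect an average increase in the viral suppression proportion over the 3 follow-up visits", the increase being "16.0% from 24.0% assumed in the control arm to 40.0% in the coached-based MEI arm (odds ratio, OR 2.03), assuming a power of 85.0" percent. On numbers: "Starting with n=240 will yield an effective sample size of 204 individuals in total, or 102 in each group, available for analysis in aim 2".
- **Data Collection for Aims 2 and 3, Table 2.** After baseline, viral load is drawn at months 3, 6 and 12, and not at 9 or 18.
- **Data Analysis, outcomes.** "The primary outcome for aim 2 is durable viral suppression (HIV viral load<200 copies/mL"). No number or pattern of visits is attached to *durable*. The secondary outcome, retention, is "documented 2 or more follow-up medical visits over 12 months, treated as a dichotomous variable".
- **Data Analysis, models.** "logistic regression is used to examine whether participants who receive MEI coach are more likely to be virally suppressed". The same sentence goes on to include retention and engagement in care. GEE is then used to see whether assignment "predicts differences in retention for the coached-based MEI versus the SOC groups using repeated measurements over a 12-month period". The next sentence says in general terms that GEE serves the longitudinal data because it handles within-person correlation. It names no outcome.

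**The concern.** The sample size rests on a repeated-measures quantity, the "average increase in the viral suppression proportion over the 3 follow-up visits". The model text does not name a repeated-measures model for that outcome. It names logistic regression, the usual model for one binary value per person, and the word *durable* points the same way. The only aim 2 outcome to which GEE is tied by name is retention, which by its own definition is observed once per person and has nothing repeated to model. For aim 3 the same section does name GEE for PrEP use over time, so the authors make the distinction elsewhere.

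This is the primary efficacy test of one of the two trials. A visit average, a single-visit value and suppression at every visit are different estimands with different power. If the text leaves the choice open, it can be made after results are seen, and the stated power holds for only one of the choices.

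**Working it through.** **Inputs.** From Sample Size Considerations: 24% vs 40%, 100 per arm (n=200) or 102 per arm (204 analyzable), power 85%. From Table 2: 3 post-baseline viral loads. Assumed, because the article does not give them: two-sided alpha 0.05 and the within-person correlation ρ, shown as a range.

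**Formula.** With d = 0.16 and mean proportion 0.32,

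power = Φ{[d − 1.96·√(2·0.32·0.68/n)] / √[(0.24·0.76 + 0.40·0.60)/n]}.

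For the average of 3 equally correlated visits, n is replaced by n / [(1+2ρ)/3].

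**1. Reproducing the stated 85%: visit average.** At ρ = 0.5 and 100 per arm, the effective n is 100/0.667 = 150. Then (0.16 − 1.96·0.0539)/0.0531 = 1.03, and power is 84.7%.

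| ρ | 100 per arm | 102 per arm |
|---|---|---|
| 0.3 | 91.6% | 92.1% |
| 0.4 | 88.3% | 88.9% |
| 0.5 | 84.7% | 85.4% |
| 0.7 | 77.7% | 78.5% |

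Exactly 85% needs ρ = 0.49 (100 per arm) or 0.51 (102 per arm). The stated figure is therefore consistent with a repeated-measures calculation at ρ near 0.5.

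The printed odds ratio differs slightly from the printed rates: (0.40/0.60)/(0.24/0.76) = 2.11, not 2.03. An odds ratio of 2.03 implies 39.1% in the MEI arm, and 85% then needs ρ of about 0.39 to 0.40.

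**2. One value per person at the stated rates.** At 100 per arm, (0.16 − 1.96·0.0660)/0.0650 = 0.472, and power is 68.2%. At 102 per arm it is 69.0%. A one-sided test reaches only 79%. For 85% two-sided,

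[1.960·√(2·0.32·0.68) + 1.036·√(0.1824+0.2400)]² / 0.16² = 151.1,

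so 152 per arm, or 304 analyzable. At 15% loss that is 304/0.85, about 358 enrolled, against the planned 240.

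**3. Suppressed at all three visits.** The article gives neither this definition nor a rate for it, so this is an illustration only. Take a latent-normal model with visit rates 24% and 40% and the same latent correlation in both arms.

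| Latent correlation | Binary correlation (approx.) | Rates | Power, 102 per arm |
|---|---|---|---|
| 0.45 | 0.27-0.29 | 6.1% vs 15.5% | 58% |
| 0.7 | 0.47-0.49 | 10.4% vs 22.1% | 62% |
| 0.9 | 0.70-0.71 | 16.0% vs 29.7% | 65% |

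If the binary correlation, rather than the latent one, is set equal in the two arms (0.3 to 0.7), the range at 100 per arm is 52-61%. Neither version approaches 85%.

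**The case against.** Several points on the other side are fair.

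- **The general GEE sentence may be meant to cover viral load.** It can be read that way, and the section also plans a time-by-treatment interaction for both aims. But the sentence names no outcome. On that reading suppression would have two models and no stated primary one.
- **Logistic regression is valid for a once-per-person durable outcome.** This is correct. In that case the model is sound and the power statement is at fault, because 24% and 40% are visit averages and not rates of durable suppression.
- **The visit rule for durable may stand in the full protocol or analysis plan.** It may, and its absence is not the point here. The point is that the printed power basis, outcome and model disagree.

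Four stronger readings are tempting, and the article does not support them:

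- *The two models were simply swapped.* The logistic sentence also covers retention, so retention has both models and suppression has one.
- *Type I error is inflated because three visits would be stacked as independent rows.* Nobody proposes that, and the section says that repeated measurements on one person are correlated and must be allowed for.
- *There are three competing primary analyses.* Retention is secondary, so its GEE is not one of them.
- *Durable suppression has 69% power.* That figure applies the visit-average rates to a different outcome.

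**Conclusion.** The mismatch stands. The article powers aim 2 on a visit average, names durable suppression as primary, and names logistic regression for it. No passage names the powered analysis for the primary outcome.

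The 85% requires joint use of the three visits with within-person correlation of about 0.5 or less. At 0.7 it is 78%. A once-per-person analysis at the printed rates has 68-69%. An all-visits outcome has roughly 58-65% under the common-latent-correlation illustration, and somewhat less under the alternative version.

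These figures assume a two-sided 5% level and, where visits are combined, equal correlation between visits. The correlation behind the 85% is not printed, so the agreement at 0.5 is strong but indirect evidence of how the figure was obtained. Separately, a GEE with repeated measurements cannot be applied to retention as it is defined, although it could be if retention were defined per interval.

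**What to change.** Settle on one primary test for aim 2, before outcomes are compared by arm. Either choice is legitimate, but the three passages must agree.

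1. **Match the sample size.** Name as the single primary test a logit-link GEE, clustered on person with robust standard errors, of viral load below 200 copies/mL at months 3, 6 and 12. Its estimand is the visit-averaged MEI vs SOC contrast. State the correlation and alpha behind the 85%, and reconcile the odds ratio with the rates. Report a defined durable outcome as secondary.
2. **Or keep durable suppression as primary.** Define it per person by visit, keep logistic regression, state the assumed durable rates in each arm, and recompute power from them.

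In both cases keep logistic regression for retention, and remove the retention GEE or define retention by interval.

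The cost is a few sentences and no new data collection. The second choice also means stating a lower power, or a larger sample, unless the assumed durable rates support the planned 240.

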##### Study Sample

YBLMSM or YBLTW, recruited into aim 1, who are identified as HIV-positive (previously diagnosed with HIV—self-report of HIV-1 and confirmed viral load, or newly diagnosed—no prior history of HIV and rapid HIV test positive) are invited to participate in the RCT of aim 2 of the study. Additional eligibility includes not virally suppressed; no plan to relocate in the next 18 months; not enrolled in another HIV treatment intervention; and currently own or have access to a cell phone, private tablet, or laptop. Potential participants are provided information about the study, consented, and a blood sample for the viral load is obtained (if no recent viral load within 3 months was documented in the medical chart). Participants with an HIV-1 viral load>200 copies/mL are eligible to participate in aim 2. We aim to recruit 240 YBLMSM or YBLTW living with HIV who are not virally suppressed.

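### The aim 2 suppression analysis does not prespecify adjustment for baseline viral load or newly versus previously diagnosed status, and so gives up a modest amount of power

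*Protocol article*

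**What the plan says.** All references are to the protocol article; Data Analysis means the section that follows Sample Size Considerations.

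- **Primary model.** Data Analysis states that "logistic regression is used to examine whether participants who receive MEI coach are more likely to be virally suppressed". Treatment assignment is described as the main independent variable in all models. No baseline covariate is named for the suppression model.
- **When covariates enter.** The same section compares the arms at baseline and adjusts for differences if they turn out not comparable. It then describes further models, stratified by age group and presented as going past intention to treat, which "include potential confounders and predictors such as prior exposure to case management and PrEP", along with sexual risk and demographics. Viral load and timing of diagnosis are not among the examples.
- **What is known before randomization.** Under Aim 2, Study Sample, each entrant is either previously diagnosed or newly diagnosed, the latter meaning "no prior history of HIV and rapid HIV test positive". Entry requires a viral load above 200 copies/mL, from a new draw or a chart value no more than 3 months old. Under Study Procedures, randomization follows enrollment and the baseline survey. The first column of Table 2 also ticks the row "Provide blood for HIV-1 RNA viral load testing (aim 2) or HIV-1 antibody testing (aim 3").
- **What randomization balances.** Only site and age group (Study Procedures; Data Collection for Aims 2 and 3).
- **Sample size.** "A total estimate of n=200 will be enough to detect an average increase in the viral suppression proportion over the 3 follow-up visits", from 24% to 40%, with 85% power.

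**The concern.** Both variables are plausible predictors of later suppression. A newly diagnosed participant is about to start care, whereas a previously diagnosed participant with an unsuppressed load has already fallen out of care or failed to respond to it. Neither variable is balanced by design. A rule that adjusts only on observed imbalance leaves them out when the arms look alike, yet adjusting for a prognostic variable raises power in balanced arms too. The rule also makes the meaning of the reported odds ratio depend on the data: marginal if no adjustment is triggered, conditional if it is.

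Accrual makes lost power costly: 36 of the 240 participants planned for aim 2 were enrolled at the time of the article.

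**Working it through.** **Inputs from Sample Size Considerations.** 24% versus 40% suppression averaged over 3 follow-up visits; 200 analysed (100 per arm); 85% power; "We expect a 15.0% loss to follow-up over 1 year in aim 2".

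**Assumed, because the article does not state them.** Two-sided alpha 0.05; an exchangeable within-person correlation ρ; the share of outcome variance explained by the covariates, R².

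**1. The plan's own figure.**
- Loss to follow-up: 240 × 0.85 = 204, or 102 per arm, as stated.
- Single-visit comparison with pooled variance under the null: n per arm = [1.960 × √(2 × 0.32 × 0.68) + 1.036 × √(0.24 × 0.76 + 0.40 × 0.60)]² / 0.16² = (1.293 + 0.674)² / 0.0256, which rounds up to 152. With 100 per arm, power is 68.2%.
- Mean of 3 visits: multiply n by (1 + 2ρ)/3. Setting 152 × (1 + 2ρ)/3 = 100 gives ρ = 0.49. At ρ = 0.5 the requirement is 102 per arm, and 100 per arm gives 84.7% power. So 200 participants at 85% power is consistent with ρ of about 0.49 to 0.50, which the article does not state.
- Aside: 24% and 40% give an odds ratio of (0.40/0.60)/(0.24/0.76) = 2.11, not the printed 2.03. This does not affect the present point.

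**2. Effect of adjustment, approximate.** With ρ set so that 100 per arm matches 152 in the single-visit formula, adjustment multiplies the variance by (1 − R²). Effective n per arm is then 152/(1 − R²), and the number needed for 85% power is about 200 × (1 − R²).

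| R² | Power | Total N for 85% power |
|---|---|---|
| 0 | 85.2% | 200 |
| 0.02 | 85.9% | 196 |
| 0.05 | 87.0% | 190 |
| 0.10 | 88.7% | 180 |
| 0.15 | 90.4% | 170 |
| 0.20 | 92.0% | 160 |

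The gain is 0.7 to 6.8 points.

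**3. Check by simulating the logistic model.** One visit, 100 per arm, 4,000 runs per scenario, 30% newly diagnosed (assumed).

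| Log-odds per SD of log10 viral load | Odds ratio, new diagnosis | R² (control arm) | Power unadjusted | Power adjusted | Variance ratio, standardized risk difference |
|---|---|---|---|---|---|
| 0 | 1 | 0 | 68.2% | 68.3% | 1.01 |
| −0.3 | 1.5 | 0.02 | 68.0% | 69.0% | 0.99 |
| −0.5 | 2 | 0.06 | 67.3% | 70.8% | 0.94 |
| −0.7 | 2 | 0.10 | 68.3% | 73.9% | 0.92 |
| −1.0 | 3 | 0.18 | 67.2% | 76.0% | 0.81 |

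In the prognostic scenarios the standard error of the log odds ratio rose on adjustment, from 0.314 to between 0.322 and 0.359, while the estimate moved from about 0.76 to between 0.79 and 0.95. The gain therefore shows as power, or as precision of the standardized risk difference, and not as a smaller log-odds standard error.

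A three-visit simulation (102 per arm, correlation about 0.4, 30% newly diagnosed) took new-diagnosis odds ratios of 2, 3 and 4 with viral-load slopes of −0.3, −0.5 and −0.7. Power rose from 87.9% to 88.8%, 89.3% to 92.1%, and 89.7% to 93.6%; with no covariate effect it was 86.5% and 86.7%.

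**4. Chance imbalance.** The standard deviation of the between-arm difference in mean log10 viral load, in units of its own SD, is √(2/n per arm): √(2/102) = 0.14 at the planned size and √(2/18) = 0.33 at 36 participants.

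**The case against.** The strongest reply is that this is a condensed article, and a covariate list is commonly left to the analysis plan. Treatment is called the primary independent variable, not the only one, and the list of predictors for the later models is given by example. That is fair as far as it goes. But the article does more than stay silent: it states the condition on which covariates enter the main analysis and sends other predictors elsewhere. If the analysis plan already fixes these covariates, confirming it closes the point.

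Three stronger readings are tempting, and the article does not support them.

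- A reader might infer that the two variables are excluded outright and that the estimate is left exposed to any imbalance in them. It is not so: the comparability rule could admit either one. The objection to the rule is that it depends on the data and does nothing when the arms look balanced.
- A reader might describe viral load as the baseline value of the primary outcome. The outcome is binary, below 200 copies/mL, and every entrant is above 200. All start with the same value of the outcome; only the degree of viremia varies. That may limit its prognostic strength, as may chart values up to 3 months old.
- A reader might infer that the unadjusted analysis is biased or invalid. It is neither.

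The small-sample argument also cuts both ways. If aim 2 stayed at 36, 36 × 0.85 is about 31 analysed, and at a mean rate of 32% about 10 would be suppressed at any one visit. Extra terms would then not be free.

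**Conclusion.** The point holds as a matter of efficiency. The suppression analysis has no fixed adjustment for two variables already established before randomization, and its stated rule leaves them out when the arms look balanced. On the planned 85%, the power forgone is roughly 1 to 7 points for R² of 0.02 to 0.20, equivalent to needing about 196 down to 160 participants instead of 200. It is nil if the variables are not prognostic, and the simulations show no loss of power from including them in that case at the planned size.

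The size rests on assumed values for R², the 30% newly diagnosed share, ρ and two-sided alpha of 0.05; none is in the article. No calculation was made for aim 3. The argument there is that past PrEP users are eligible (only current use is excluded), PrEP history is collected in the aim 1 survey, and Data Analysis itself treats prior PrEP exposure as a predictor, but only in the later models.

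**What to change.** State in the analysis plan that, whatever the observed balance:

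- the aim 2 suppression model includes log10 pre-randomization viral load (the screening draw or the qualifying chart value), newly versus previously diagnosed status, and the randomization strata of site and age group;
- the result is reported as a standardized (marginal) risk difference and odds ratio, so that the 24% versus 40% contrast used for the sample size is unchanged;
- the aim 3 primary model includes history of PrEP use.

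This fixed list should replace adjustment triggered by observed imbalance. The cost is a few lines of wording and a few more model terms, with no new data collection. The extra terms matter only if the final aim 2 sample stays very small, so the list should be kept short in that event.
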